## Abstract

**Background:**

Cognitive behavioral therapy (CBT) is considered a first-line treatment for posttraumatic stress disorder (PTSD) but is rarely available in regular care. Action is clearly needed to increase treatment availability. A possible solution to improve access to treatment would be the use of remotely delivered digital intervention. Internet-delivered CBT may also carry several other advantages compared to traditional psychological treatments (e.g., less therapist time per patient, bridging geographical distances between therapist and patient, and provision of a standardized intervention). In a pilot study conducted within a psychiatric outpatient setting, a digital therapist-guided prolonged exposure program (Huddinge Online Prolonged Exposure; HOPE) demonstrated preliminary effectiveness, patient acceptability, and feasibility. This project will build upon these findings and evaluate whether HOPE is effective in reducing PTSD symptoms.

**Method:**

The study is a randomized controlled superiority trial, with assessors masked to treatment allocation. Two hundred eighty-six participants will be randomly allocated to receive either 10 weeks of HOPE or an active control condition (therapist-guided internet-delivered psychoeducation, relaxation, and support). The primary outcome is the severity of symptoms of PTSD for the last month measured by the clinician-administered PTSD scale for DSM-5 (CAPS-5). Secondary outcomes include self-rated measures of symptoms of PTSD and complex PTSD, depression, quality of life, cost effectiveness, mediators of change, dropout rates, and adverse events.

**Discussion:**

This study will be the first to compare digital prolonged exposure (HOPE) with an active control condition and not exclude patients with severe or complex PTSD. The strength of the study is that it is conducted in a clinical setting with wide eligibility criteria and the use of gold-standard measures to assess outcomes. Potential challenges in the execution of the trial include participant recruitment, retention, and adherence to treatment and therapist retention.

**Trial registration number:**

Clinicaltrials.gov; NCT05934162. Registered 6th July 2023. Open Science Framework https://osf.io/dsg9p/. Registered 2nd September 2023.

## Background {6a}

Posttraumatic stress disorder (PTSD), as defined in the Diagnostic and Statistical Manual of Mental Disorders, Fifth Edition, is a debilitating psychiatric condition characterized by distressing symptoms such as intrusions of the traumatic event, inability to be around trauma reminders, cognitive and mood changes, and arousal symptoms and is associated with considerable functional impairment and comorbidity [1]. PTSD is one of the most common psychiatric disorders, with an estimated lifetime prevalence of approximately 5.6% [2] If left untreated, extensive data show a significantly increased risk for substance use, suicidality, and poorer mental health/functioning [3, 4] as well as impaired physical health [5].

Individual trauma-focused CBT, such as prolonged exposure (PE), is considered a first-line treatment for PTSD is recommended as a first-line treatment for adult PTSD across major guidelines, including NICE, the 2023 VA/DoD guideline, and the APA clinical practice guideline but is seldom available in regular care [6]. Given the large group of afflicted and the treatment gap, action is clearly needed to increase availability. A possible solution to improve access to evidence-based treatment would be the use of remotely delivered digital treatment. Internet-delivered CBT may also carry several other advantages compared to traditional psychological treatments (e.g., less therapist time per patient, bridging geographical distances between therapist and patient, and provision of a standardized intervention). Recently, the NICE Early Value Assessment recommended two digital treatment programs for adults with mild to moderate PTSD based on the results of two large randomized controlled trials, for use in the NHS while further evidence is generated. The first study (RAPID, *n* = 196) showed that internet-delivered therapist-guided CBT was noninferior to face-to-face CBT treatment at 16 weeks, with improvements maintained to 52 weeks [7]. The other study (STOP-PTSD, *n* = 217) demonstrated that internet-based therapist-guided cognitive therapy for PTSD was superior to internet-based stress management therapy at 13 weeks, with outcomes and cost-effectiveness assessed through 26 and 39 weeks [8]. PE has thus far been evaluated in a digital format in two previous settings, among military personnel and veterans in the USA (Web-PE; [9]) and for recently traumatized individuals in the general Swedish population (Condensed internet-delivered prolonged exposure CIPE; [10, 11]).

This project is the first large RCT to evaluate therapist-guided digital PE for PTSD and not exclude severe cases of PTSD and complex PTSD as often seen in psychiatric settings.

## Objectives {7}

The main objective of the trial is to test whether our newly developed digital treatment (Huddinge Online Prolonged Exposure; HOPE) is more effective than the active comparator in reducing PTSD symptoms. The trial will also include a health-economic evaluation from both the treatment provider perspective (i.e., direct costs such as costs for healthcare personnel) and a broader societal perspective (i.e., indirect costs such as sick leave). We will also investigate processes of change during treatment and predictors of treatment outcome.

## Trial design {8}

The trial uses a single-blind (blinded assessors), randomized (1:1), controlled, parallel-group, superiority design comparing 10 weeks of either therapist-guided HOPE to an active control condition for adults with PTSD residing in Sweden. We aim to recruit 286 participants who will be assessed pretreatment, during treatment, posttreatment, and 1 month after treatment completion (primary endpoint). Naturalistic follow-up will be conducted at 6- and 12-month follow-ups. The Consolidated Standards of Reporting Trials (CONSORT) flow chart of the trial is shown in Fig. 1. The data analytic plan was published on the Open Science Framework (OSF) before data collection began.

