### Criteria for discontinuing or modifying allocated interventions {11b}

Participants may withdraw their consent to participate in the treatment and the trial at any timepoint. Suicidal ideation triggers a structured suicide-risk assessment (e.g., C-SSRS plus focused interview on intent, plan, means, and protective factors) and, if indicated, referral. All safety assessments are conducted remotely (telephone or secure video), no face-to-face visits are planned. The intervention may be temporarily titrated or discontinued for (a) acute suicide risk requiring urgent care or (b) emergent medical/psychiatric conditions that render participation unsafe. Acute risk is managed per the study safety protocol with immediate escalation and referral to regular care (e.g., emergency psychiatric services, local outpatient psychiatry, emergency department). Participants who discontinue the intervention are invited to continue all scheduled outcome assessments when clinically appropriate.

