### Outcomes {12}

The primary outcome measure is the CAPS-5, the gold-standard clinical interview that evaluates the severity of PTSD symptoms and determines the presence of PTSD in the past month [12]. This evaluation will be conducted at multiple time points: upon enrollment, 1 month after completing the treatment (primary endpoint), and during the 6- and 12-month follow-up assessments. The CAPS-5 total severity score has been shown to exhibit strong internal consistency (Cronbach’s *α* = 0.88) and interrater reliability (intraclass correlation coefficient = 0.91), along with favorable test–retest reliability (intraclass correlation coefficient = 0.78) [12]. Treatment response will be considered achieved if there is a minimum of 10 points improvement on the CAPS-5 between baseline and the participant’s last available measurement within the baseline to 12-month follow-up period (adapted from [13]). Remission will be defined as the absence of a PTSD diagnosis or a CAPS-5 total symptom severity score below 12 [13]. To be classified as having achieved recovery, participants must maintain their remission status at both the 6-month and 12-month follow-ups.

Secondary self-rated outcome measures include the Posttraumatic Stress Disorder Checklist for DSM-5 (PCL-5) [14] and the International Trauma Questionnaire (ITQ) [15] to capture self-rated symptoms of PTSD and complex PTSD. The Patient Health Questionnaire (PHQ-9; [16]) and the EuroQol 5-dimensions (EQ-5D; [17]) will be used to assess the level of depressive symptoms and quality of life. Treatment response on the PCL-5 will be defined as a drop of 10 points or more. For remission, a score below 30 will be used, which has been identified as indicative of probable PTSD in the Swedish version of the PCL-5 [18].

To calculate quality-adjusted life-years for cost-utility analysis, participants will complete the Assessing Quality of Life 6 Dimensions (AQoL-6D; [19]). Data concerning the utilization of medical resources, medication, social care, absenteeism, and presenteeism in relation to employment will be collected using The Treatment Inventory of Costs in Patients with psychiatric disorders (TIC-P; [20]). Moreover, information on adverse events will be gathered using the Negative Effects Questionnaire (NEQ) immediately after treatment completion and the upcoming assessment points [21]. Participants will also receive an open-ended question asking for the occurrence of adverse events weekly during treatment.

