#### Treatment variables

Data will also be collected on the number of completed modules, dropouts of treatment, sent messages, and therapist time spent in the digital platform for each participant and any additional time needed, for example, phone calls outside the platform. A treatment completer is defined as a participant who completed all treatment modules or responded early. Early recovery is defined as the participant showing a positive response after completing at least 3 modules, with a minimum of a 10-point reduction on the PCL-5 or achieving a total sum score below 30, and both the participant and therapist agreeing to conclude the treatment. Participants who discontinue treatment or experience early recovery will be encouraged to continue their participation in the remaining outcome assessment points.

Ratings on the subjective units of distress (SUD) will be collected during exposure exercises (pre, during, post and maximum), and harm expectancies will be assessed using digital worksheets. The Credibility/Expectancy Questionnaire (CEQ; [22]) and Working Alliance Inventory–Short Form Revised (WAI; [23]) will be utilized to assess treatment credibility and working alliance between the treatment arms.

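### The primary CAPS-5 visit is counted from treatment completion, which an early response can bring forward; the text does not fix a common assessment time

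*Protocol article*

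**What the plan says.** Two sections define the primary endpoint, and both count from the end of treatment. Trial design {8} has "1 month after treatment completion (primary endpoint"); Outcomes {12} has "1 month after completing the treatment (primary endpoint"). The section on assessment and collection of outcomes {18a} also ties the post-treatment assessment to completion.

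The Treatment variables section says what completion means: "A treatment completer is defined as a participant who completed all treatment modules or responded early". The early route is open to anyone "showing a positive response after completing at least 3 modules". For this the PCL-5 must have fallen by 10 points or more, or stand under 30, and participant and therapist must both agree to stop. Both programmes have six modules over a nominal 10 weeks.

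For those who stop treatment, section {11b} says: "Participants who discontinue the intervention are invited to continue all scheduled outcome assessments when clinically appropriate". Table 2 shows one column for weeks 1–10, followed by the 1-month, 6-month and 12-month columns. It gives no week number for the primary visit, and neither it nor the text gives a visit window or a rule for participants who conclude early.

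**The concern.** Put together, the stated anchor and the stated definition of a completer make the date of the primary assessment depend on how well the participant has done. Someone with a good PCL-5 score halfway through may be assessed weeks earlier after randomisation than someone who uses the full 10 weeks. Someone who discontinues never reaches the event from which the visit is counted.

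For the individual, the link between timing and response is direct. Between arms it is indirect: the early-conclusion rule is the same in both, so mean timing differs only if response rates or pace differ. The superiority hypothesis expects response to differ. The decision to conclude is shared by the participant and the therapist, neither of whom is blinded.

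CAPS-5 "determines the presence of PTSD in the past month", so a shift in the visit moves the whole period being rated. The primary model treats time as nominal visits, and the article describes no allowance for elapsed time. What is at stake is a clean reading of the 1-month contrast: part of any difference could reflect when people were assessed.

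**Working it through.** **The plan's own figure.** With d = 0.35, two-sided α = 0.05 and 80% power, n per arm = 2(1.960 + 0.842)²/0.35² = 128.2, rounded up to 129, as stated in Sample size {14}. Dividing 129 by 0.90 gives 143.3; the article uses 143 per arm (143 × 0.9 = 128.7), 286 in total. The sample size is not in dispute and does not change below.

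**Timing.** Inputs: 6 modules in 10 weeks (Intervention description {11a} and Comparator) and a minimum of 3 modules (Treatment variables). Assumption: even pace, so 10/6 = 1.67 weeks per module. One month is 30.4/7 = 4.34 weeks.

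| Treatment ends after | End (week) | Primary CAPS-5 (week) | Shift (weeks) |
|---|---|---|---|
| 3 modules | 3 × 1.67 = 5.0 | 9.3 | 5.0 |
| 4 modules | 4 × 1.67 = 6.7 | 11.0 | 3.3 |
| 5 modules | 5 × 1.67 = 8.3 | 12.7 | 1.7 |
| 6 modules | 10.0 | 14.3 | 0 |

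Five weeks is therefore the largest shift at an even pace. At that extreme the past-month windows (weeks 5.0–9.3 and 10.0–14.3) do not overlap.

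**Effect on the contrast.** The article gives neither early-conclusion rates nor a rate of symptom change after stopping. Both are assumed here.

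Shift in contrast = (share concluding early in HOPE − share in control) × CAPS-5 drift over the period of the shift.

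- Low: (0.20 − 0.10) × 0.05 SD = 0.005 SD, which is 0.005/0.35 = 1.4% of the planned effect.
- High: (0.30 − 0.10) × 0.20 SD = 0.04 SD, which is 0.04/0.35 = 11.4%.
- Equal shares (0.10 in both arms): no shift in the mean.

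The drift of 0.05–0.20 SD over 5 weeks equals 0.01–0.04 SD per week. A wider set of assumptions (up to 50% v 20% early, mean shift of 2 to 5 weeks, same weekly drift) gives 0.002 SD to (0.50 − 0.20) × 5 × 0.04 = 0.06 SD wherever the rates differ.

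**Effect on power.** With 129 per arm, nominal power is 80% at d = 0.35. A shift of 0.005 SD moves it to 79% or 81%; 0.04 SD to 70% or 88%; 0.06 SD to 64% or 91%. Which side applies depends on the direction of drift. If early concluders are still improving, an early visit understates their gain; if they later relapse, it overstates it. The document does not say which to expect.

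**The case against.** The strongest reply is that the article can be read as having a fixed schedule. Treatment is defined as 10 weeks, Table 2 shows one treatment block followed by the same visits for all, and people who stop are invited to scheduled or remaining assessments, which presupposes a timetable that continues without them. The early-recovery rule appears where completers are classified and does not itself set visits. Visit windows may also be laid out in the full analysis plan.

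Much of this stands. It means the text does not establish that early responders are in fact assessed early. It does not remove the conflict: the two sections that define the primary endpoint state an anchor, that anchor is completion, and nothing says that early concluders wait until week 10. This is a stated rule that needs correcting or qualifying, not a detail left to another document.

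Three stronger readings are tempting, and the document does not support them:

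- That intention-to-treat is broken. Participants are analysed by intention to treat and retained after stopping; uneven timing blurs what is estimated but does not undo the comparison.
- That timing is known to differ by arm. The rule is common to both arms, and no early-conclusion rates are given.
- That earlier access to the other condition distorts the primary result. Access opens only after the primary visit, and later follow-up is labelled naturalistic.

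**Conclusion.** The point holds as an unresolved conflict in the definition of the primary endpoint. Taken literally, the anchor allows the primary CAPS-5 to fall up to about 5 weeks early for early responders and leaves discontinuers without a stated date. That 5 weeks is a maximum, resting on an even pace and a stop at the minimum of three modules. Applying it to every early concluder, as the illustrative 0.005–0.04 SD does, tends to overstate the effect under those assumptions. The rates and drift are assumed throughout, and the direction is unknown. The likely bias is small beside d = 0.35, but it concerns the primary endpoint and is avoidable, so the wording should be corrected.

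**What to change.** In {8}, {12} and Table 2, define the primary assessment as a fixed time from randomisation or from a fixed treatment start date (10 weeks plus 1 month), with a visit window. Apply it to every participant, whatever the number of modules completed and whether treatment was concluded early or discontinued. Time the 6- and 12-month visits from the same date.

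For participants already assessed, report the actual time from randomisation to the primary CAPS-5 by arm, and add a sensitivity analysis that accounts for it. Modelling elapsed time as continuous and estimating the contrast at the common target week is preferable to adding elapsed time as a covariate, because it arises after randomisation and may be linked to response.

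Cost: if practice already uses a fixed week, this is a clarifying sentence. If visits have been counted from completion, it is a modification to be disclosed on the Open Science Framework and in the trial registry. Because inclusion began in September 2023, the primary endpoint may then contain two timing rules, which is why actual timing should be reported. No extra visits or participants are needed. The clinical rule for concluding treatment early and the rule for access to the other condition need not change.

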**Fig. 1 Fig1:**
[figure not shown]
CONSORT flowchart

The research study received ethical approval from the Swedish Ethical Review Authority under ID 2023-02329-01 and was preregistered on both Clinicaltrials.gov and OSF before the commencement of data collection. The reporting of data will adhere to the guidelines set forth in The Consolidated Standards of Reporting Trials statement for nonpharmacological trials (CONSORT) and the Consolidated Health Economic Evaluation Reporting Standards (CHEERS) regardless of the study’s outcome. The trial will adhere to the principles of Good Clinical Practice (GCP).

## Methods

### Study setting {9}

The trial will take place in a publicly funded outpatient psychiatric clinic in Stockholm, Sweden. Self-referral is possible through a dedicated secure study site.

### Eligibility criteria {10}

We will employ broad eligibility criteria to maximize the external validity of the study. Participants with comorbid conditions, such as neuropsychiatric disorders, depression, and substance abuse, will be considered for inclusion provided they meet all other inclusion/exclusion criteria, with PTSD being their primary diagnosis. Eligibility is determined via a two-stage process: (1) a participant-completed web-based screening battery for common mental disorders (including PTSD symptoms, depression/anxiety, alcohol/drug use, psychosis/mania, and suicidal ideation), followed by (2) a clinician-administered diagnostic assessment to confirm PTSD and evaluate risk.

Please see Table 1 for the full inclusion and exclusion criteria.

**Table 1 Tab1:** Inclusion and exclusion criteria

**Inclusion criteria**	≥ 18 years of age
	Primary diagnosis of PTSD according to the Diagnostic and Statistical Manual of Mental Disorders, fifth edition (DSM-5)
	Signed informed consent
	Have had a stable dose of any psychotropic medication for at least 4 weeks prior to study entry
	Being fluent in Swedish
	Daily access to a computer or device with internet connection
**Exclusion criteria**	PTSD is not the primary concern
	Serious mental health symptoms, such as mania, psychosis, alcohol, or substance use disorders or current suicide risk warranting immediate clinical attention
	Ongoing trauma-focused CBT or Eye movement desensitization and reprocessing therapy
	Ongoing trauma-related threat (e.g., living with a violent spouse)

### Informed consent {26a}

During the self-referral process, informed consent will be obtained through a secure study platform utilizing a two-step authentication system.

### Additional consent provisions for collection and use of participant data and biological specimens {26b}

This trial does not involve collecting biological specimens for storage.

## Interventions

### Explanation for the choice of comparators {6b}

The trial will compare therapist-guided digital prolonged exposure (HOPE) to a digital therapist-guided active control condition to assess its efficacy. A matched digital comparator preserves parity in modality, platform, therapist contact, and expectancy, enabling estimation of the incremental benefits and potential adverse effects attributable to trauma-focused exposure. The comparator includes psychoeducation, stress-management skills, and supportive therapist contact, and explicitly excludes imaginal and in vivo exposure and other trauma-focused techniques. After the 1-month post-treatment follow-up (primary endpoint), participants may access the alternative condition without therapist guidance. This timing preserves the integrity of the primary endpoint while improving ethical access.

### Intervention description {11a}

Prolonged exposure is considered one of the first-line treatments for PTSD and is recommended in available treatment guidelines [6]. In this trial, PE is delivered digitally as HOPE, a therapist-guided, internet-based program over 10 weeks comprising six sequential modules [11]. Modules are content packages rather than single “sessions”: participants work with each module across several days or weeks, completing multiple practice exercises within and between modules. The treatment mirrors face-to-face PE in structure and components, psychoeducation, in vivo exposure, imaginal exposure with processing, and relapse-prevention planning and progression is driven by practice completion and clinical milestones.

## Comparator

Active control will use established CBT interventions such as psychoeducation about trauma and PTSD, relaxation, stress management techniques, and controlled breathing but will not include any exposure. The treatment will be given in a digital format with therapist support and consist of six sequential treatment modules that the participants are expected to complete in 10 weeks.

